## Abstract

**Background:**

Significant racial, ethnic, and socioeconomic disparities exist in access to evidence-based treatment services for children with autism spectrum disorder (ASD). Patient Navigation (PN) is a theory-based care management strategy designed to reduce disparities in access to care. The purpose of this study is to test the effectiveness of PN a strategy to reduce disparities in access to evidence-based services for vulnerable children with ASD, as well as to explore factors that impact implementation.

**Methods:**

This study uses a hybrid type I randomized effectiveness/implementation design to test effectiveness and collect data on implementation concurrently. It is a two-arm comparative effectiveness trial with a target of 125 participants per arm. Participants are families of children age 15–27 months who receive a positive screen for ASD at a primary care visit at urban clinics in Massachusetts (*n* = 6 clinics), Connecticut (*n* = 1), and Pennsylvania (*n* = 2). The trial measures diagnostic interval (number of days from positive screen to diagnostic determination) and time to receipt of evidence-based ASD services/recommended services (number of days from date of diagnosis to receipt of services) in those with PN compared to and activated control -Conventional Care Management – which is similar to care management received in a high quality medical home. At the same time, a mixed-method implementation evaluation is being carried out.

**Discussion:**

This study will examine the effectiveness of PN to reduce the time to and receipt of evidence-based services for vulnerable children with ASD, as well as factors that influence implementation. Findings will tell us both if PN is an effective approach for improving access to evidence-based care for children with ASD, and inform future strategies for dissemination.

**Trial registration:**

NCT02359084 Registered February 1, 2015.

## Background

### Evidence-based services for autism spectrum disorder

Over 15 years of data support the notion that earlier access to evidence-based services (EBS) improves both short and long-term outcomes for children with autism spectrum disorder (ASD) [1]. Studies consistently demonstrate that intensive early intervention improves cognition, language skills, and reduces the core symptoms of ASD [2–4], and that earlier access to these services leads to both immediate benefits, and gains over time [5].

### Disparities in autism services

Significant disparities exist in access to EBS for children with ASD. On average, low-income and minority children with ASD are diagnosed later than their white and higher income counterparts, and they experience substantial delays in initiating treatment – even after diagnosis [6, 7]. Because earlier access to evidence-based ASD services improves both short and long-term outcomes, delayed engagement with these services can be responsible for substantial morbidity [8]. Obtaining an ASD diagnosis and engaging with treatment involves a number of complex steps, including visits with a primary care provider for screening, visits with a subspecialist for diagnosis, receipt of an individually-tailored treatment plan, and ongoing early intervention and special education support [9]. Barriers to timely ASD diagnostic and treatment services can result from a variety of factors including the availability of services, patient-provider miscommunication, parental stress, complex payment systems, and culturally biased care [10–12].

### Patient navigation

Patient Navigation (PN) is a theory-based and empirically-supported care management strategy designed to reduce disparities in access to care, and thus represents a promising strategy to help low-income and minority families access timely evidence-based ASD services. PN focuses on overcoming patient-specific barriers to a defined set of services over a time-limited period. It is rooted in the Chronic Care Model [13], and has empiric evidence in diseases such as cancer and HIV as a means to reduce disparities in outcomes [14–16] by shortening the interval between a positive screening test (for example, a mammogram for breast cancer) and definitive diagnosis. Early pilot data demonstrate that PN has the potential to reduce the time from initial ASD screening to diagnosis, and to improve access and retention in treatment services [17].

### Rationale for hybrid design

Despite the promise of PN as a stretgy to reduce disparities in access to EBS for this population, multiple studies show that access to new innovations, particularly in mental health, is often significantly delayed for low-income and minority populations [18]. This gap in equitable access to evidence-based care has led leaders in healthcare policy to call for research that specifically addresses the adoption and spread of innovations – like PN – that promote engagement with treatment services for vulnerable patients [19]. Consistent with this concern, multiple studies in cancer and HIV demonstrate varying success or diminution of impact of PN upon implementation in real-world practice [20–22]. Therefore, the current protocol describes a hybrid implementation-effectiveness trial in which we will evaluate both the effectiveness of PN, while at the same time assessing factors that influence its implementation. The purpose of this trial design is to prepare for the rapid dissemination of PN as a strategy to reduce disparities in ASD engagement in EBS, if proven effective.

## Methods/design

### Overview

This study compares PN to Conventional Care Management (CCM) on two primary outcomes - diagnostic interval and time to receipt of evidence-based ASD/recommended services. A number of secondary outcomes such as number of children diagnosed with ASD, satisfaction with the navigator, and an array of parent-reported measures (e.g. parenting stress, social support, and coping responses) will be evaluated as well. Using a mixed methods approach (process mapping, qualitative, and quantitative data analyses), we will also assess implementation of PN, with a focus on identifying failures in implementation, why they exist, and how to mitigate them for future adoption and spread. Our study is designed as a type I hybrid effectiveness/implementation evaluation to provide the evidence needed for patients, clinicians, and policy makers to determine if PN should be offered to children at risk for ASD in primary care, and how it can be spread to clinical practice after the trial is complete. The study protocol described received approval from the Boston University Institutional Review Board (protocol number H-33008). See Fig. 1 for full CONSORT diagram.

**Fig. 1 Fig1:**
[figure not shown]
CONSORT diagram

### Conceptual framework

Our intervention is informed by the Chronic Care Model, which identifies six fundamental areas that form a system that encourages high-quality chronic disease management (self-management support, delivery system design, decision support, clinical information systems, organization of health care, and community) [23]. The model was developed to help systems create supportive interactions between an informed, activated patient and a prepared, proactive practice team. Our navigation strategy uses the following principles of the Chronic Care Model: 1) navigators are trained in community and health system resources for ASD to allow for integration of services across sectors; 2) navigators are trained in motivational interviewing and collaborative decision making to support proactive interactions between patients and providers. Our implementation evaluation is guided by the Consolidated Framework for Implementation Research (CFIR) developed by Damschroder and colleagues [24], and preliminary data from Drahota and colleagues’ Autism Model of Implementation (AMI) [25], which also draws from CFIR. We will assess PN across all five domains of CFIR (Intervention Characteristics, Outer setting, Inner setting, Characteristics of Individuals, Process), by exploring multiple constructs from each domain. We chose CFIR because it has two specific advantages over other determinant frameworks that apply to the current project: 1) CFIR offers an overarching typology to promote theory development and verification about what works where and why across multiple contexts. Therefore it is most appropriate for formative work, in which specific causal mechanisms for implementation success are not hypothesized a priori; 2) CFIR contains a broad range of contextual dimension (5 domains and 26 discrete constructs) that describe the internal and external context of implementation. Therefore it is particularly suitable for studying implementation in multiple settings and diverse populations.

### Setting

The setting for this hybrid type I randomized effectiveness/implementation study is three urban primary care networks affiliated with Boston Medical Center (BMC), Children’s Hospital of Philadelphia (CHOP), and Yale University (Yale), and their Developmental and Behavioral Pediatrics (DBP) autism specialty clinics. Each DBP clinic is a member of the HRSA-funded DBPNet – a 12-site practice-based research network whose mission is to conduct collaborative, interdisciplinary research in developmental and behavioral pediatric settings. Clinical sites include three types of primary care practices – hospital, community, and health center – and are located in three states (Massachusetts, Connecticut, and Pennsylvania) with different requirements for accessing ASD services. These sites serve a diverse population of over 7000 children in the target age range each year.

### Participants

Because our study is designed to test a strategy to reduce disparities, our recruitment efforts focus on urban, racial and ethnically diverse populations - who historically report low levels of engagement with the healthcare system - within our three study sites. Participants will be children 15 to 27 months with a positive The Modified Checklist for Autism in Toddlers, Revised with Follow-Up (MCHAT-R/F) screen at their health supervision visit, or those who are referred by their pediatrician based on clinical concern. The MCHAT-R/F is a 2-stage parent-report screening tool to assess risk for ASD. The initial screen is performed in the primary care pediatrician’s office and consists of 20 yes/no questions. The scores range from “low risk” (0–2), “medium risk” (3–7), or “high risk” (8–20). Children who score “high risk” or “medium risk” are referred to our study by the primary care physician. Children who are “high risk” are screened for enrollment into the study. Children who are “medium risk” are administered a follow up interview (per MCHAT-R/F protocol) by study staff, and are referred to the study if positive. Because this is designed as a pragmatic trial, inclusion criteria are broad. Specific inclusion criteria are as follows: 1) Age 15–27 months at time of referral; and 2) MCHAT-R/F score demonstrating risk for ASD or provider concerns for ASD. The only exclusion criteria is a prior diagnosis of ASD. There are no exclusions based on language spoken or co-morbid condition.

### Control and intervention groups

#### Control

The control arm of this study receives Conventional Care Management consistent with the type of care provided within a traditional - but high quality – medical home. The care manager is available by phone to provide families with phone numbers and resources related to parents’ concerns about their child’s appointment, diagnosis, or developmental services.

The care manager contacts families by phone after randomization to introduce herself and remind families of their first appointment at the developmental clinic for their child’s ASD evaluation. The child’s primary care clinician also receives a letter from the care manager informing the clinician that the family has been assigned a care manager. The letter also contains the care manager’s contact information. After the care manager’s introductory phone call and letter, she remains available to the child’s family and other members of the care team if and when they initiate contact.

### Intervention

PN is a theory-based, empirically-supported, multicomponent, manualized care management strategy [26, 27]. It differs from other care management strategies in that it focuses on overcoming patient-specific barriers to a defined set of services over a defined, time-limited period. PN is well established in cancer care as a means to reduce disparities in the critical interval between a positive screening test (for example, a mammogram for breast cancer) and definitive diagnosis [16, 17, 28], decrease anxiety [29], and increase satisfaction with services [29]. The goal of PN is to integrate a disjointed health care system on behalf of an individual patient. In our proposal, we build upon the established principles of PN but expand the navigator role in novel ways. Navigation services are provided to the family unit by bilingual paraprofessionals. It is extended to integrate a fragmented network of ASD services that requires coordination among community-based and educational services, as well as those provided by the conventional health care team.

Additionally, PN is augmented with evidence-based behavior change strategies – motivational interviewing and collaborative decision making – that support patient engagement and self-management skills. A typical PN activity may be to assist a parent with marginal literacy to complete a clinic’s patient questionnaires, help a family know what to expect during a stressful ASD diagnostic evaluation, or coordinate childcare around a child’s early intervention schedule. In this proposal, the systemic PN protocol begins after referral for an autism evaluation and end 100 days after diagnostic resolution – at which time, a child with ASD would be expected to be engaged and retained in intensive early intervention services (based on the guidance from Autism Speaks) [30]. Navigators follow a standardized protocol, keep extensive structured logs of their work, and a random subset of encounters are audio recorded. Data are captured on all interactions with families, providers, medical, educational, and social service organizations, recording time spent, activities performed, and barriers addressed.

### Randomization process

We use stratified, blocked (randomly varying blocks of 2 and 4) randomization to allocate participants to Navigation or CCM. Randomization occurs independently at each primary care recruitment site. Randomization lists are generated in a secure web-based data management system. All outcome assessors are blinded to participant allocation. Written and verbal informed consent is obtained by research staff prior to randomization. Data will be collected in stored in StudyTrax, a commercial clinical research data management tool.

### Effectiveness outcomes

#### Primary outcomes

The study’s primary outcomes are access to screening, diagnostic, and evidence-based service outcomes (Table 1). The trial measures diagnostic interval (number of days from positive screen to diagnostic determination) and time to receipt of ASD services/recommended services (number of days from date of diagnosis to receipt of services) from review of child’s medical and early intervention records in those with PN compared to CCM.

**Table 1 Tab1:** Diagnostic and Service Outcomes (primary outcomes)

Outcome	Measures	Response	Description
Expedited Evaluation	Achievement of Diagnostic Resolution	Yes/No	Percent children who complete diagnostic assessment within 12-month follow-up
	Timing of Diagnostic Resolution	Timely	Timely- Diagnostic interval ≤ 120 days
		Delayed	Delayed- Diagnostic interval > 120 but ≤ 180 days
		Unresolved	Unresolved - No resolution by 12-months
	Diagnostic Interval	Number of Days	Beginning the day of the positive confirmatory screen and ending the day when family receives determination (yes/no) of ASD diagnosis
Referral to Treatment	Time to receipt of EI services	Number of Days	Days from failed M-CHAT to receipt of services
	Time to receipt of ASD services	Number of Days	Days from Date of diagnosis to ASD services
Engagement in Treatment	Hours of services	Number of Hours	Hours ASD specialty services
	Adequacy of Services	Yes/No	Based on guideline of 25 h/ week
	Absenteeism	Number of absences	Number of family-initiated “no show” and cancellations divided by the number of scheduled appointments in 6 month period following diagnosis
Determination of ASD Diagnosis	ASD diagnosis	Yes/No	Based on ADOS evaluation by Board Certified DBP
Satisfaction with ASD-Services	Client Satisfaction Questionnaire [50]	Categorical and numerical	Previously validated measure of satisfaction with services
	Satisfaction with Hospital Care Questionnaire [50]	Categorical and numerical	Previously validated measure of satisfaction with services
Satisfaction with Navigator	Patient Satisfaction with Interpersonal Relationship with Navigator [51]	Categorical and numerical	Newly validated 9-item scale to assess satisfaction with the interpersonal relationship with navigators

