### Analyses

#### Intervention main effects

We will conduct an intention-to-treat (ITT) analysis where the denominator will include all children randomized to a treatment arm. For categorical outcomes we will use logistic regression models to compare the proportion of children who completed the diagnostic evaluation, and received recommended ASD specific services.

For time-to-event outcomes (time to diagnostic resolution, and time to receipt of ASD services) we will use censored analyses to construct Kaplan-Meier curves of time to event, and estimate hazard ratios, using Cox proportional hazard models.

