#### Completion of diagnostic evaluation

In our pilot work, 50% of children who are referred for developmental evaluations complete the evaluation. We aim for a 90% completion rate, which is consistent with our pilot PN study data and assume a marginal improvement in the CCM arm to 65%. With the expected sample, we will have > 90% power to detect clinically significant differences by treatment arm in ITT and explanatory analyses.

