#### Time to receipt of recommended services

We assume that 80% in PN arm and 60% in the CCM arm will receive ASD services 5 months after a failed M-CHAT screen. A log rank test will have over 80% power to detect such differences as clinically significant at the 0.05 level.

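### Time to services, the second primary outcome, starts at diagnosis, so children never diagnosed have no start time and the promised all-randomized Cox analysis cannot be done as defined

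*Protocol article*

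**What the plan says.** The service outcome is one of two primary outcomes (Methods/design, Overview). It is defined three times, each time with diagnosis as time zero:

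- Abstract, Methods: "number of days from date of diagnosis to receipt of services".
- Primary outcomes, text: "time to receipt of ASD services/recommended services (number of days from date of diagnosis to receipt of services".
- Table 1: "Days from Date of diagnosis to ASD services".

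Intervention main effects sets the analysis population: "We will conduct an intention-to-treat (ITT) analysis where the denominator will include all children randomized to a treatment arm". For the time-to-event outcomes, and it names time to ASD services as one of them, "we will use censored analyses to construct Kaplan-Meier curves of time to event, and estimate hazard ratios, using Cox proportional hazard models". It gives no start time for a child who is never diagnosed. Table 1 expects such children, since it has a category for no resolution by 12 months.

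PN starts before diagnosis, after referral for evaluation (Intervention). The power section expects it to change who is diagnosed: it aims for 90% completion of the evaluation under PN and, for the control, the authors "assume a marginal improvement in the CCM arm to 65" per cent.

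The power statement for services uses another clock. It assumes that 80% of PN and 60% of CCM children "will receive ASD services 5 months after a failed M-CHAT screen", and claims over 80% log-rank power.

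**The concern.** The definition and the analysis population cannot both hold. A clock that starts at diagnosis has no time zero for an undiagnosed child, so that child cannot be in the risk set. The Cox comparison, run on the outcome as defined, is confined to children who reached a determination.

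That subset forms after randomization, at the step PN is meant to improve. The two diagnosed groups need not be alike, because the PN group includes families whom CCM would have lost. The better PN does on the first primary outcome, the further the second departs from a randomized comparison. A primary hazard ratio labelled intention-to-treat would then carry selection bias, and neither a favourable nor an unfavourable result could be attributed to PN with confidence.

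The power section adds a second problem, because its clock starts at the failed M-CHAT. The stated power therefore does not describe the endpoint that the article defines.

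**Working it through.** **Inputs from the article.** 125 children per arm; two-sided alpha 0.05; diagnostic completion 90% v 65%; services received 80% v 60% at 5 months after the failed M-CHAT.

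**1. The plan's own power.** The proportions imply a hazard ratio of ln(1 − 0.80)/ln(1 − 0.60) = 1.756. Expected events, keeping all 250 children: 125 × 0.80 + 125 × 0.60 = 175. Schoenfeld: z = √175 × 0.5 × ln(1.756) − 1.96 = 1.77, power 0.96. The Freedman formula gives 0.95 and a two-proportion test 0.94. The claim of over 80% is correct on the failed-M-CHAT clock with every child retained. The completion claim also holds: 90% v 65% gives power 0.998 against the stated figure of over 90%.

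**2. Who has a start time on the diagnosis clock.**

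- PN: 125 × 0.90 = 112.5; without a start time, 12.5.
- CCM: 125 × 0.65 = 81.25; without a start time, 43.75.

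About 194 of 250 children can enter and about 56 cannot, most of them from CCM.

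**3. Comparability of those who enter.** Assume monotonicity: every child diagnosed under CCM would also be diagnosed under PN. Then 65% are diagnosed in either arm, 25% only under PN and 10% in neither. The share of diagnosed PN children with no CCM counterpart is 25/90 = 28%.

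**4. Illustration with no PN effect after diagnosis.** Let b be the proportion served within 5 months of diagnosis among children diagnosed in either arm, and q the proportion among children diagnosed only under PN. Both are assumptions on the diagnosis clock. Diagnosed CCM children show b; diagnosed PN children show (0.65b + 0.25q)/0.90.

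| b | q | PN | CCM | PN minus CCM (points) |
|---|---|---|---|---|
| 60% | 60% | 60.0% | 60% | 0 |
| 60% | 40% | 54.4% | 60% | −5.6 |
| 60% | 20% | 48.9% | 60% | −11.1 |
| 80% | 80% | 80.0% | 80% | 0 |
| 80% | 60% | 74.4% | 80% | −5.6 |
| 80% | 40% | 68.9% | 80% | −11.1 |
| 80% | 20% | 63.3% | 80% | −16.7 |

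The sign can reverse: b = 60% and q = 80% give (0.39 + 0.20)/0.90 = 65.6%, a spurious gain of 5.6 points.

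For b = 60%, a log-rank simulation (3,000 trials per scenario, exponential times, all determined children counted, follow-up cut at 150 days) rejected in 4.8% of trials at q = 60%, 13% at 40%, 22% at 30% and 35% at 20%.

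**5. Illustration with a true effect.** Suppose PN raises service receipt from 60% to 80% in children diagnosed in either arm. With q = 80, 60, 40 and 20%, the observed difference is 20, 14.4, 8.9 and 3.3 points, and two-proportion power is 0.86, 0.57, 0.25 and 0.07.

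**6. Power if 80% v 60% is carried over to the diagnosis clock.** Events: 112.5 × 0.80 + 81.25 × 0.60 = 138.75. Power is 0.91 (Schoenfeld) or 0.86 (two proportions) if every determined child counts. If only children with ASD count, Schoenfeld power is 0.81, 0.64 or 0.43 at assumed ASD shares of 75, 50 or 30%. The article gives no such share.

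**The case against.** **The plan already has all-randomized service comparisons.** This stands. The logistic regression on receipt of recommended services needs no diagnosis date and can count undiagnosed children as not served. Table 1 also measures early intervention services from the failed M-CHAT. A reader might infer that the trial loses every intention-to-treat comparison of services. It does not: the fault is confined to the time-to-service outcome and its hazard ratio. But that outcome is primary, and the logistic model does not repair it.

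**The analysis section states no time origin, and the power section's clock would keep undiagnosed children at risk.** True, and an unseen analysis plan may use that clock. The outcome definition is nevertheless explicit in three places. The conflict is in what is written, so it is not a detail left for later.

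**The bias is not shown to run against PN.** This stands. A reader might infer that the hazard ratio will make navigation look worse, on the ground that families reached only through PN are harder to connect to services. That is plausible, but nothing in the article says so. The bias is zero if those families reach services as quickly as the others, and it favours PN if they do so faster.

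**Power is not shown to be inadequate.** This also stands. A reader might infer from step 6 that the diagnosis-clock analysis is underpowered. That conclusion needs an ASD share that the article does not give; with all determined children counted, power stays above 80%. Nor would higher power on an all-randomized clock show power lost on the same question, because that comparison also contains PN's effect on diagnosis.

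**Children found not to have ASD may still have an event.** The outcome covers recommended services as well as ASD services, so it would be too strong to say that they never can. A determination date is still required, so the start-time problem remains.

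**Conclusion.** The point holds as a contradiction within the article that affects a primary outcome. Followed as written, the time-to-service hazard ratio compares about 112 PN with 81 CCM children selected after randomization, and it is not an intention-to-treat result. These counts follow from the plan's own figures; the 28% without a counterpart also needs monotonicity. The distortion could be nil, or could reach about 11 points (60% base) or 17 points (80% base) against PN over the ranges tried. Those service rates are assumptions, and the article settles neither size nor direction. The stated power is arithmetically sound, but for a different endpoint.

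**What to change.** Use one clock for the primary time-to-service outcome in the Abstract, Primary outcomes, Table 1, Intervention main effects and the power section. Either randomization or the positive screen would serve. Randomization is the simpler choice, because children may also enter on provider concern and might then have no positive-screen date.

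Suggested wording: *Time to services is the number of days from randomization to first receipt of ASD or recommended services, analysed in all randomized children. Children remain at risk whether or not a diagnostic determination has been made, and are censored at loss to follow-up or at end of follow-up.*

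Then:

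- State which services count for a child found not to have ASD. If only ASD services count, treat a non-ASD determination as a competing event and report cumulative incidence by arm.
- Restate the 80% v 60% assumption and the power on the chosen clock.
- Report the diagnosis-to-service interval among diagnosed children as supportive and explicitly non-randomized.

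Cost: the outcome then combines delay before and after diagnosis and overlaps the first primary outcome, so an effect on diagnosis alone would move both; the supportive interval helps to separate them. The change to a primary outcome must be recorded in the registration, before outcomes are examined by arm. The plan already draws on medical and early intervention records, but the team should confirm that service dates are sought for undiagnosed children over the same follow-up, since the article does not describe this.
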